#### Program Fidelity

We will take the following measures to ensure the program is delivered with high quality and good fidelity. First, all research staff will receive 2 months of intensive, project-specific training on research ethics, intervention design, and project implementation. They will also receive training on interviewing patients and research conduct at the family medicine clinics where the intervention will take place. Health coaches will receive additional training on how to interact with patients, how to demonstrate the use of the Fitbit Flex 2, and how to set short-term goals and track progress on the iCanFit online community. They will practice health coaching with patient representatives from our CAB until satisfactory performance is demonstrated. We will also have refresher training once a year during the project implementation. Second, health coaches will counsel patients under the supervision of a registered nurse; an experienced nurse will randomly check these counseling sessions and provide timely feedback. As part of quality control, our CAB will conduct site visits quarterly throughout the study. Third, the principal investigators of the project will work in the participating clinics for quality assurance and address any issues that may come up during the trial.

#### Patient Retention

To ensure we retain most of the patients during the intervention trial, the following measures were proposed. First, we will explain to the participants the longitudinal nature of the study during the informed consent and the fact that they will have a phone survey in 3 months and a follow-up clinic visit in 6 months. Second, 2 weeks prior to the follow-up survey or visit, we will remind the participants via SMS text message or phone call and help them schedule the appointment at their convenience. Third, for patients who do not comply with the intervention protocol, for example, do not wear the Fitbit constantly or do not sync the data in a timely fashion, we will send friendly reminders via SMS text message and motivate them with positive outcomes of physical activity and social support from the iCanFit community. Patients who continuously ignore our reminders and invitations—for 2 consecutive weeks—will be considered dropouts. We expect a 20% attrition rate at 6 months. Fourth, some participants might lose their Fitbit device during the trial. We will immediately replace a Fitbit if lost. Based on our prior experiences [35,36], less than 5% of participants may lose the mobile device during the trial. Finally, some overweight older adults may report discomfort in exercise. During the counseling by the health coach at baseline, we will advise participants to slowly increase their physical activity level and to monitor their heart rates. All participants will have a brochure of safety tips (see Multimedia Appendix 3) outlining typical adverse events and how to take appropriate actions in case of such an event. The patient is advised to go to the nearest emergency room for an event that needs immediate care. For nonurgent issues that require consultation with a PCP, the health coach will assist to schedule an appointment.

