**Figure 4 figure4:**
[figure not shown]
Process of comparator protocol (for patients in the control group). PCP: primary care provider.

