#### Comparator

The patients in the control group will receive usual care enhanced with a Fitbit Flex 2, as shown in Multimedia Appendix 2. The Fitbit Flex 2 was released in 2016, costs US $75, and weighs a quarter of an ounce. It is compatible with iPhones and Android phones, only needs to charge once a week, syncs automatically with mobile phones within 20 feet, and easily syncs to a computer with a USB port. It tracks steps taken, stairs climbed, calories burned, distance travelled, and sleep time. Figure 4 illustrates the process of the comparator protocol. After eligible patients provide informed consent, they will first complete an HBA on an iPad while waiting for their appointment. Unlike patients in the intervention group, patients in the control group will not receive any reports from their HBA; after their appointment with the PCP, they will receive a Fitbit Flex 2 and a brochure explaining how to use the Fitbit and the benefits of regular physical activity. Patients in the control group will not be given any information about the iCanFit online community; neither will they receive counseling or monitoring from health coaches. Similar to the intervention group, control group patients will receive the safety tips of exercise brochure.

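### The dropout rule counts ignored Fitbit reminders as loss to follow-up and probably applies more often in the intervention arm than in the control arm

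*Protocol article*

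**What the plan says.** All of this is in the protocol article.

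- **Patient Retention** opens for the whole trial: "To ensure we retain most of the patients during the intervention trial". The second measure reminds participants two weeks before each follow-up contact, with no restriction by arm.
- The third measure covers device use. Reminders go out "for patients who do not comply with the intervention protocol, for example, do not wear the Fitbit constantly or do not sync the data" in good time, and they "motivate them with positive outcomes of physical activity and social support from the iCanFit community". The dropout rule comes next: "Patients who continuously ignore our reminders and invitations", for two weeks running, are counted as dropouts. The following sentence is "We expect a 20% attrition rate at 6 months".
- **Comparator** limits what controls receive: "Patients in the control group will not be given any information about the iCanFit online community", and "neither will they receive counseling or monitoring from health coaches". The caption of Figure 4 names their pathway: "Process of comparator protocol (for patients in the control group".
- **iCanFit 2.0 Intervention Protocol** describes four steps for the intervention arm. These include continuous coach monitoring of Fitbit use and a coach call after two idle weeks.
- **Power and Sample Size Calculations** makes weekly minutes of moderate-to-vigorous activity (MVPA), taken from the Fitbit, the primary outcome. **Outcome Measures and Sources of Data** sets a phone survey at 3 months and a clinic visit at 6 months.

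**The concern.** Two things are run together. Not wearing a device, or not answering texts about it, is non-adherence. Loss to follow-up means that outcome data can no longer be obtained. The rule turns the first into the second after two weeks of silence.

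The rule also depends on being sent something to ignore. If wear and sync reminders go only or mainly to the intervention arm, its patients have many more occasions to be labelled, and dropout counts would not mean the same thing in the two arms. That matters here because the Discussion already expects that controls may have more attrition, so a reader will want to compare attrition by arm.

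The same reminders act on the instrument that records the primary outcome. Encouraging activity is part of the intervention, but more complete recording of activity in one arm is not a treatment effect. If labelled patients were also left out of follow-up or analysis, the randomised comparison would be restricted by behaviour after randomisation.

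**Working it through.** **1. Which arm gets the wear/sync reminders?**

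For intervention only:
- The section titled iCanFit 2.0 Intervention Protocol describes the intervention arm, and the control pathway has its own name in the Figure 4 caption.
- The reminder content draws on a community that controls are not told about.
- Controls have no coach monitoring.
- The limitations in the Discussion say that controls lack regular monitoring and social support.

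For both arms:
- Patient Retention opens for the whole trial and names no arm.
- Both arms have the Fitbit.
- The Discussion uses the term intervention protocol for a design whose listed strengths include the control-arm Fitbit.

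Intervention only is better supported but not certain. If both arms are meant, the community content still cannot go to controls without contradicting Comparator, and the idle calls remain in one arm.

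**2. How can a patient meet the rule?**

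| Route | Intervention | Control |
|---|---|---|
| Wear/sync reminders | Yes, whenever wear or sync lapses | Not on the better-supported reading |
| Reminders before the 3- and 6-month contacts | Yes, 2 occasions | Yes, 2 occasions |

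The rule can therefore operate in controls, but on fewer occasions.

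**3. What can a labelled patient still provide?**

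The 3-month survey, SF-12 quality of life and 6-month weight need no Fitbit. MVPA does: without wear and sync there are no valid MVPA data for that period, whichever visits are kept. Attendance and missing MVPA are separate facts and need separate counts.

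**4. The only scale in the article.**

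- 398 × 1.25 = 497.5, stated as 498.
- 498 / (1 − 0.2) = 622.5, stated as 622.
- Allowance: 622 − 498 = 124 patients. Per arm: 622 / 2 = 311, and 311 × 0.20 = 62.2, about 62.

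This is a planned loss, not a bias. The power section takes its 0.2 from a prior trial, not from this rule.

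**5. Illustration under assumptions that are not in the article.**

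Suppose that labelled dropouts were excluded, and that they were less active than completers by g SD. The completer mean in an arm with dropout fraction p exceeds the full-arm mean by p × g, so the contrast shifts by g × (p_int − p_ctl).

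| p_int / p_ctl | g = 0.25 | g = 1.0 |
|---|---|---|
| 20% / 20% | 0 | 0 |
| 15% / 25% | −0.025 | −0.10 |
| 10% / 30% | −0.05 | −0.20 |

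Swapping the arms reverses the sign. The target effect is 0.25 SD. The direction is not known: the rule would label more intervention patients, while the Discussion expects more control attrition.

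Power is hardly affected if overall attrition stays at 20%. Take SE = √[1.25 × (1/n_int + 1/n_ctl)], d = 0.25 and the one-sided 5% test that reproduces 398. Then 20%/20% gives 0.802 and 10%/30% gives 0.797. Any harm would be to bias and interpretation.

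**The case against.** The strongest reply is that Patient Retention names no arm and that both arms wear the device, so the text may describe one trial-wide procedure in loose words. That reading is possible. It reduces the prompting concern to the community content and the idle calls, but dropout would still be defined by ignored messages.

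Second, a reader might infer that the rule cannot apply to controls at all. The article does not support this. The rule covers invitations as well as reminders, and the reminders before follow-up contacts go to all participants. The supportable claim is unequal exposure to the rule.

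Third, a reader might infer that labelled patients are removed from follow-up or from the primary analysis. Nothing says so. The Data Analysis Plan describes a repeated-measures multi-level model and excludes nobody on this ground. The risk is that the label comes to be used in that way.

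Fourth, coach monitoring is part of the planned contrast, and non-wear rules are commonly left to fuller documents. Both points stand. Neither the coach calls nor the lack of a non-wear rule is criticised here. What is criticised is a rule that the article does state.

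Finally, replacing the rule by a missed 6-month visit would not be enough, because a patient can attend that visit with no MVPA data. This is correct, and the fix below takes account of it.

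**Conclusion.** The point holds in limited form. The stated rule classes non-adherence as dropout, whichever arm receives the reminders. With medium confidence, it also applies more often in the intervention arm. That part rests on reading the intervention protocol as the intervention arm's procedure, which the section titles, the Figure 4 caption and the limits on controls favour without settling.

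The size of any bias cannot be computed, because the article gives no wear rate and no mean or SD for MVPA. The shifts of 0.025 to 0.20 SD in the illustration rest wholly on assumed attrition by arm, an assumed activity gap and an assumed exclusion of labelled patients. They show scale only and should not be quoted as an estimate. The change is worth making because the wording can produce dropout counts that are not comparable between arms, and correcting it costs almost nothing.

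**What to change.** 1. **Definition, both arms.** Define study dropout as withdrawal of consent or loss to follow-up. Record ignored reminders and non-wear as non-adherence. Keep contacting these patients for the 3- and 6-month assessments and analyse them as randomised. Report missing Fitbit MVPA by arm, separately from missed visits. The cost is a change of protocol wording and continued contact with patients who do not respond to reminders.

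2. **Reminders, preferable but secondary.** State the arm for each kind of reminder. Send one neutral wear/sync message on the same trigger in both arms, for example after a sync gap whose length the investigators set. Keep community content and coach calls in the intervention arm. The cost is one SMS template, checks of control-arm sync gaps by someone other than the health coaches, and a comparator slightly stronger than the device alone. The idle calls would still leave some difference in prompting, which is part of the intervention being tested.

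The article reports that the trial is not yet funded, so both changes can be made before recruitment.

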#### iCanFit 2.0 Intervention Protocol

As illustrated in Figure 3, the iCanFit 2.0 intervention protocol includes four steps. First, after the eligible participants complete the informed consent forms, they will complete an HBA on an iPad (see Multimedia Appendix 1 for sample screenshots), which takes about 15 minutes. Right after completion, patients will receive a printed copy of the HBA summary report with colorful charts of their current level of physical activity compared to the recommended physical activity levels (see sample summary reports in Multimedia Appendix 1). Meanwhile, the same report will be printed out in the office of the PCP with whom the patient has an appointment. Second, the patient brings the HBA report into his/her appointment with the PCP and the report serves as a natural conversation starter to facilitate patient-provider communication and joint goal setting. Third, right after the patient’s appointment with the PCP in the primary care clinic, a health coach will meet with the patient, further explain the HBA report, and ensure the patient has set a long-term physical activity goal, if the patient has not set one with the PCP. The health coach will give the patient a Fitbit Flex 2 (Fitbit Inc) (see Multimedia Appendix 2 and section below about the device) and demonstrate how to use the device. The health coach will also help the patient to create an account on the iCanFit online community. The health coach will advise on how to set short-term (eg, weekly) goals, track and sync data, share progress with family and friends via Facebook, and obtain personalized feedback on the iCanFit online community. The counseling session will last 30 minutes; a photo-illustrative brochure with instructions on how to use the Fitbit as well as account information and reminders will be given to the patient. Fourth, the health coach will constantly monitor patients’ use of the Fitbit and iCanFit online community. Patients will receive incentives (eg, online badges, virtual coins, and honor levels) for meeting physical activity goals and updating their progress. Any questions posted on the iCanFit online community will be answered by the health coach within 12 hours. If a patient is “idle” for 2 weeks, the health coach will call the patient to offer help and address the patient’s barriers. Patients will also receive a brochure of safety tips (see Multimedia Appendix 3), which details possible adverse events during exercise and how to take action depending on the situation. For adverse events that need immediate medical attention, patients are advised to go to the nearest emergency room. For nonurgent matters, they can contact the health coach, who can assist with scheduling a clinic appointment with the patient’s PCP.

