1. iCanFit 2.0 is a complex intervention with multiple components; it requires buy-in from the primary care clinics and especially the PCPs. It also requires skilled coordination and joint efforts by multiple parties.2. iCanFit 2.0 needs well-trained health coaches for counseling and monitoring of the patients.3. Some older patients may not have Internet access either via computers or mobile phones and, therefore, may not be able to join the study.4. The control group does not have regular monitoring and social support and may suffer a higher rate of attrition.5. The iCanFit online community needs active users to maintain the positive social norm, which may be challenging for older adults. It merits further study on how to further engage older adults and obtain social support online.

Despite these limitations, to the best of our knowledge, the iCanFit 2.0 intervention will be one of the first multi-level, mobile-enabled, physical activity-promotion programs for older adults in a primary care setting. It was built upon our 10 years of research of a mobile-based intervention to promote physical activity in older adults. We have engaged patients and other key stakeholders throughout the design and will continue to do so in the intervention trial.

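### The two-week rule defines dropout by non-adherence, through reminders tied to the intervention; it may cause avoidable, arm-dependent loss, or it conflicts with the comparator

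*Protocol article*

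**What the plan says.** All references are to the protocol article.

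- **Patient Retention.** Reminders by text message are planned "for patients who do not comply with the intervention protocol, for example, do not wear the Fitbit constantly or do not sync the data" promptly. They are meant to "motivate them with positive outcomes of physical activity and social support from the iCanFit community". The rule follows: "Patients who continuously ignore our reminders and invitations—for 2 consecutive weeks—will be considered dropouts". The next sentence expects 20% attrition at 6 months.
- **Comparator.** Control patients also receive a Fitbit, but "Patients in the control group will not be given any information about the iCanFit online community". On coaching, the same section adds: "neither will they receive counseling or monitoring from health coaches".
- **iCanFit 2.0 Intervention Protocol.** In the intervention arm "the health coach will constantly monitor patients’ use of the Fitbit and iCanFit online community", and "If a patient is “idle” for 2 weeks, the health coach will call the patient to offer help".
- **Power and Sample Size Calculations.** The primary outcome is weekly minutes of moderate-to-vigorous physical activity (MVPA) taken from the Fitbit. The baseline sample is the number needed divided by (1 − 0.2) for attrition.
- **Outcome Measures and Sources of Data.** Quality of life and self-reported activity come from surveys, with a phone follow-up at 3 months and a clinic visit at 6 months. Weight comes from the health record.
- **Discussion, limitations.** "The control group does not have regular monitoring and social support and may suffer a higher rate of attrition".

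**The concern.** A patient who stops wearing or syncing the device and does not answer messages has stopped adhering. That patient has not withdrawn consent, died or missed an assessment. Calling this dropout merges non-adherence with loss to follow-up, and sites are likely to stop pursuing a patient they have classed as gone. Any data lost that way cannot be recovered by a later analysis plan.

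The route into dropout status also runs through reminders that are worded for the intervention arm. If only that arm can meet the rule, the two arms lose patients by different mechanisms. Because the primary outcome comes from the same device whose non-use triggers the reminders, that loss may be related to outcome. If the rule is meant for both arms, the reminder as described tells controls about a component that the Comparator section withholds from them. The passages need reconciling under either reading.

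**Working it through.** **1. How the plan treats dropouts in its numbers.** The stated chain is 398 → 498 → 622.

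- 398 × 1.25 = 497.5, rounded to 498.
- 498 / (1 − 0.2) = 622.5, stated as 622.
- 622 − 498 = 124 patients are therefore budgeted as giving no usable outcome.

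The last step is the one that matters here: attrition is treated as complete loss. (The starting 398 is close to the 396 that a one-sided 5% normal-approximation test gives; a two-sided test gives 504. The 20% is dated to 6 months under Patient Retention and to 12 months in the sample size section. Both are separate matters.)

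**2. Which data the rule puts at risk.**

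| Data | Needs Fitbit wear and sync? | Obtainable from a non-responder to reminders? |
|---|---|---|
| MVPA (primary) | Yes | Only for periods worn and synced |
| Quality of life, self-reported activity | No | Yes, if the patient is contacted |
| 6-month visit | No | Yes, if the patient attends |
| Weight in the health record | No | Yes, if weighed at a clinic visit |

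**3. Which arm the rule can reach.**

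- *Intervention arm only.* The reference to the intervention protocol, the community theme and the coach monitoring all fit this reading. One arm then has an adherence-based route to dropout that the other lacks.
- *Both arms.* The text speaks of patients in general, controls have a Fitbit, and the reminder before each survey or visit goes to all participants. But the adherence reminder invokes the community, against the Comparator section, and checking wear and sync sits badly with a control group that the Discussion describes as not regularly monitored.

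**4. Illustration of size if the loss were one-sided.** The inputs are assumptions; the documents give neither. Let x be the extra share of the intervention arm lost, taken as its least adherent patients, and ρ the correlation between adherence and MVPA. For a normal adherence score, the mean of those remaining shifts by

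bias (SD) = ρ × φ(z_x) / (1 − x),

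where φ is the standard normal density and z_x its x-quantile. For x = 10% and ρ = 0.5, φ(z_x) = 0.1755, so 0.5 × 0.1755 / 0.9 = 0.097 SD.

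For type I error, take a simple comparison of means with no true effect, 249 completers per arm (498 / 2) and design effect 1.25: SE = √(2 × 1.25 / 249) = 0.100 SD, two-sided 5% test.

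| x | ρ | Bias (SD) | Share of d = 0.25 | Type I error |
|---|---|---|---|---|
| 5% | 0.3 | 0.033 | 13% | 6.2% |
| 5% | 0.5 | 0.054 | 22% | 8.4% |
| 10% | 0.3 | 0.058 | 23% | 9.0% |
| 10% | 0.5 | 0.097 | 39% | 16.4% |
| 20% | 0.3 | 0.105 | 42% | 18.2% |
| 20% | 0.5 | 0.175 | 70% | 41.5% |

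A cruder check agrees in order of magnitude. If a share p is lost and those patients lie 0.5 SD below their arm's mean, the shift is p × 0.5 / (1 − p): 0.056 SD at p = 10% and 0.125 SD at p = 20%.

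The bias is about zero if the rule acts equally in both arms, or if those classed as dropouts stay in follow-up and in the analysis with their outcomes observed.

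**The case against.** A reader might infer that the plan removes inactive patients selectively from the intervention arm, biases the result in its favour and breaks intention-to-treat. The article does not support that.

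- It never says that dropouts leave follow-up or the analysis. The planned mixed model can use whatever was recorded before dropout.
- It never restricts the rule to one arm. The rule also mentions invitations, and controls receive follow-up invitations too.
- Not wearing or syncing a device and not answering messages is not the same as being inactive.
- The Discussion expects that attrition may be higher among controls. The net imbalance, and so the direction of any bias, is open.
- The bias figures rest on assumed inputs and a single-time-point mean. The planned test is the group-by-time term in a repeated-measures model.
- MVPA from a device that is never worn or synced is missing whatever the patient is called.
- The coach's call after two idle weeks does not contradict the rule. The call can come first, with the reminder clock running afterwards.

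All of this stands, and it limits the claim. It does not dispose of it. The rule is stated outright and is not a detail awaiting an analysis plan. The expected attrition follows it directly and is budgeted as loss. A mixed model gives valid estimates only if missingness depends on observed data, and it cannot supply surveys that were never sought. If the rule is read as covering follow-up invitations, two weeks' silence before the 3-month survey could class a patient as a dropout well before the 6-month visit. Higher control attrition for other reasons cannot be relied on to cancel loss that arises by a different mechanism.

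**Conclusion.** The point holds in a limited form. The plan defines dropout by non-adherence after allocation and, read with the sentence that follows and the sample size calculation, counts it as loss, although several outcomes could still be collected. As worded, the rule either acts mainly in the intervention arm or conflicts with the Comparator section. It may therefore bias the comparison, but neither direction nor size is established.

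The range of 0.03–0.18 SD (13–70% of the planned effect) is an illustration only. It assumes that 5–20% of one arm is lost with no matching loss in the other, that adherence correlates 0.3–0.5 with MVPA, and that those lost contribute nothing to the analysis.

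**What to change.** 1. Delete two weeks of ignored reminders as a definition of dropout. Record it as non-adherence.
2. Define attrition identically in both arms: withdrawal of consent, death or a missed assessment.
3. Seek the 3-month survey, the 6-month visit and any available Fitbit data from every consented patient, and analyse all of them by the allocation of their clinic.
4. Reconcile Patient Retention with Comparator by stating that community-themed reminders go to the intervention arm only.

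A new wear-and-sync reminder for controls is not needed for this. It would change a comparator that the article describes as unmonitored.

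The cost is protocol wording and a few more follow-up contacts with patients already enrolled. The change will not recover MVPA from devices that are not worn or synced; that part of the primary outcome will still be missing.
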